### 2.5. Questionnaires

Participants are forwarded the scientific survey via a link/URL. The questionnaires can be answered at any time and from any chosen location via LimeSurvey [50] (LimeSurvey Cloud Version 6.6.7) using a tablet, PC, laptop, or smartphone. The questionnaires used in this study are provided in the Supplementary Materials. The survey tools were developed specifically for this research question and are grounded in the ideas of the Health Belief Model (HBM) and the Theory of Planned Behavior (TPB). These theoretical models served as a basis to define research questions and hypotheses and to develop questionnaire items. Two online surveys were developed: one for vegan participants (pregnant women and parents of vegan-fed children) and one for medical experts (physicians, pharmacists, and dieticians). All participants in each target group received the same version of the respective questionnaire. Within the survey for vegan participants, there are 10 question categories and corresponding detailed questions on the following: health (A), definition and reasons for a vegan diet (B), definition and understanding of and about DS (C), benefits, risks and expectations of DS (D), personal selection criteria of DS (E), level of knowledge about DS (F), sources of information about a vegan diet and DS (G), influential factors regarding a vegan diet and DS (H), deficiency and dosage of DS (I), and administration and compliance with DS intake (J). The questionnaire categories for the medical experts are structured similarly, but with a focus on topics related to patient and client counseling, as well as the personal views of physicians, pharmacists, and dietitians regarding a vegan diet and the intake of DS during pregnancy and childhood. Both questionnaires contain Likert scales, multiple-choice and single-choice questions, ranking questions, and an open-ended item. While most of the used response formats are common in surveys, the actual items were newly developed for the VedieS study. Because the questionnaires were developed based on the theoretical framework and objectives of the study itself, no standardized or pre-validated instruments were used, so no external approval was required. No additional statistical validation methods (such as factor analysis) were planned, as the questionnaires were not designed as psychometric tests but as data collection instruments based on the study hypotheses. To ensure content validity, a pre-test was conducted. The questionnaire was reviewed by nutritional experts, and a pretest was conducted with individuals from the target groups (vegans *n* = [20.0], medical experts *n* = [10.0]). This pretest focused on comprehension, relevance, and completion time of the items. Due to the received feedback, minor modifications for improvement were made. On average, completing the questionnaire took approximately 25 min for vegan participants and 20 min for medical experts.

### 2.6. Calculations of Case Number Scenarios

#### 2.6.1. Sample Size

This study does not follow a hypothesis-testing design with predefined effect sizes or intervention outcomes. Therefore, no formal power calculation (e.g., based on alpha level, statistical power, or expected effect size) was carried out. Instead, the sample size was determined based on population estimates, feasibility, and the exploratory character of the study.

##### Planned Sample Size for Vegan Participants

The study targets a small and hard-to-reach group whose exact size and characteristics are difficult to determine: individuals who follow a vegan diet during pregnancy or while raising their children. Although estimates suggest that 0.5–1% of the Austrian population follows a vegan diet [51], there are no official data on how many continue this diet throughout pregnancy and early parenthood. It is assumed that some individuals who usually follow a vegan diet may change their diet during these life stages, often due to concerns about nutrient adequacy, limited medical counseling, or external pressures. While exact numbers are unavailable, studies suggest that such factors may lead some vegans to modify or discontinue their diet in pregnancy or because of their children [33,52]. This uncertainty makes it particularly difficult to determine the actual size of the relevant study population. According to national birth statistics, around 400,000 children are expected to be born in Austria over a five-year period [53]. If 0.5–1% of those children are raised in vegan households, this would correspond to an estimated 2000–4000 families. The study aims to reach approximately 25% of this estimated population, resulting in a target sample of 1000 vegan participants. This sample size allows for meaningful descriptive analyses and subgroup comparisons (e.g., supplement users vs. non-users), without implying statistical representativeness.

##### Planned Sample Size for Medical Experts

For medical experts, the aim is to recruit approximately 60 participants per expert group (pediatrics, gynecology, general medicine, pharmacy, dietetics). This number was chosen because of similar studies, along with what is realistically possible, and the range of opinions expected across different medical professions [35,54,55].

Feedback from the pretest and preparation phase showed that many medical experts feel they have little or no experience with vegan patients—especially pregnant individuals or families with vegan-fed children. Hence, some may not see the topic as relevant to their work, which can affect their willingness to participate. Still, gathering a broad range of perspectives (including those who feel unsure or not directly involved) is important for the goals of the VedieS study. The planned sample size is large enough to examine differences in counseling practices, knowledge, and attitudes both within and between the professional groups.

### 2.7. Statistical Methods and Data Analysis

The survey data will first be exported from LimeSurvey to Excel (Microsoft Corp., Redmond, WA, USA) and then analyzed using IBM SPSS Statistics version 31 (IBM Corp., Armonk, NY, USA) and R version 4.5.1 (R Core Team). Descriptive statistics will be used to summarize the results. For example, averages and standard deviations will be calculated for numeric variables, while frequencies and percentages will be reported for categorical data. Diagrams such as bar charts and boxplots will visualize the results. Depending on the type of data, different methods will be used to compare groups. Categorical variables will be analyzed using chi-square tests, and continuous variables with ANOVA. For yes/no outcomes (such as whether participants use DS or whether medical experts recommend them) logistic regression models will be applied to examine possible influencing factors. We plan to use both simple (univariate) and more complex (multivariate) logistic regression models. In the multivariate models, we will include relevant background characteristics like age, gender, education, household situation, or medical profession to better account for possible confounding effects. Since the study is exploratory, *p*-values will be reported descriptively. There will be no correction for multiple testing. Comparisons between groups will be carried out only when there is a sound theoretical reason and enough data to support it.

Possible comparisons within the vegan participant group include

-People living in rural vs. urban areas;-Supplement users vs. non-users (for themselves or their children);-Participants who changed their diet during pregnancy vs. those who did not;-Individuals who received professional advice vs. those who used informal sources like social media.

Possible comparisons within the group of medical experts include

-Those who support vs. those who reject vegan diets during pregnancy and childhood;-Those who advise supplementation vs. those who discourage it;-Differences between professions (e.g., pediatricians, pharmacists, dietitians).

Depending on the final data, additional group comparisons will be added. We will only report comparisons that are well justified and provide useful insights.

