#### 2.1.1. Primary Objectives

##### Determination of Main Influential Factors That Affect Vegans Regarding Their Diet During Pregnancy and When Feeding Their Children (Up to the Age of 5 Years)

Influence by medical experts or other influences (e.g., social environment, Internet and social media, magazines) concerning the decision for or against a vegan diet should be clarified. Depending on the source of information, the possible risks of a vegan diet during pregnancy, infancy and early childhood can be misjudged.

The identification of information sources for vegans on dietary supplements, as a reason for the approval or rejection of DS (during pregnancy, infancy and early childhood), embodies trustworthiness by ranking.

It should be determined which information on DS (during pregnancy, infancy and early childhood) is used and whether this information appears trustworthy or causes uncertainty. Information received affects selection, intake, or avoidance of certain DS. The health impact of selected sources of information on DS can be made visible. Medical expert advice and other opinion-forming aspects (e.g., social environment, Internet and social media, magazines) should be ranked according to their relevance. Main sources of information should be identified.

This can be an important approach for the improvement of information supply on DS in a vegan diet and for minimizing risks preventively. By recognizing sources of information classified as the most important for vegans, the main causes of frequent inadequacies in the provision of information could be identified and if necessary, positively changed.

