## 3. Results/Outcome Measures

### 3.1. Primary Outcome Measures

Primary outcome measures include influential factors that affect how vegans approach their diet during pregnancy. Furthermore, details about decisions regarding the use of DS of vegan pregnant women and parents’ administration of DS to their children, which impacts their nutritional status and health, are essential outcomes.

Other primary outcome measures involve methods of information gathering related to a vegan diet and DS among vegans, as well as opinions and recommendations from medical experts on these topics and their advice to support or reject a vegan diet and DS. All findings will be based on the frequency and prevalence of collected responses.

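### Section 2.7 names only chi-square and ANOVA for group comparisons; if Likert items are handled as categorical, chi-square ignores their order and loses about 20 to 30 points of power

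*Protocol article*

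**What the plan says.** Section 2.7 opens its paragraph on comparisons with a general rule, "Depending on the type of data, different methods will be used to compare groups", and then fills it in: "Categorical variables will be analyzed using chi-square tests, and continuous variables with ANOVA". For binary outcomes, "logistic regression models will be applied to examine possible influencing factors". These are the only inferential methods named. P-values are to be descriptive and uncorrected for multiplicity.

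Section 2.5 describes the instrument: "Both questionnaires contain Likert scales, multiple-choice and single-choice questions, ranking questions, and an open-ended item". It does not say how many items have each format, and the questionnaires themselves are in supplementary material that is not shown.

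Section 2.6.1 plans about 60 respondents in each of five professions and regards this as enough to study differences in counselling, knowledge and attitudes within and between professions. No alpha, power or effect size is given: "no formal power calculation (e.g., based on alpha level, statistical power, or expected effect size) was carried out". Section 2.7 lists differences between professions among the intended comparisons.

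**The concern.** A Likert response is ordered. Section 2.7 has one test for categorical variables and one for continuous variables, and an ordered item belongs clearly to neither. The analyst must put it in one class or the other, and the document does not say which.

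The choice matters. Pearson chi-square gives the same result however the columns are permuted. It spreads its sensitivity over every possible pattern of difference, when the pattern of main interest is usually that one group agrees more than another. With 60 per profession there is little power to spare. A real difference in attitude between, say, paediatricians and dietitians could be reported as showing no clear signal when an equally simple test would often have found one. Leaving the classification open also means that it could be made after the data are seen.

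**Working it through.** **Plan's own figure.** There is none to reproduce, because section 2.6.1 states that no power calculation was made. The group size of 60 and the five professions come from the document. The two-sided alpha of 0.05, the item distributions, the effect sizes and the unequal splits below are assumptions.

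**Step 1: a worked case, 60 vs 60, odds ratio 2.** Take a five-point item with probabilities 10/20/30/25/15% in the first group. Its cumulative probabilities are 0.10, 0.30, 0.60 and 0.85. A proportional-odds shift of 2 divides each cumulative odds by 2:
- 0.111/2 = 0.056, giving 0.053
- 0.429/2 = 0.214, giving 0.176
- 1.5/2 = 0.75, giving 0.429
- 5.667/2 = 2.833, giving 0.739

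The second group therefore has 5.3/12.4/25.2/31.1/26.1%.

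The chi-square noncentrality is λ = n Σ(p_gj − p̄_j)²/p̄_j, summed over groups g and categories j. With n = 60, λ = 4.39 on (2−1)(5−1) = 4 degrees of freedom, which gives power of 35%. For the rank test, λ = n Σ(m_g − m̄)²/v, where m_g is the mean mid-rank score (ridit) in group g and v is its variance in the pooled distribution. This also gives λ = 4.39, but on 1 degree of freedom, so power is 55%. The signal is the same; chi-square spreads it over four times as many degrees of freedom.

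**Step 2: five professions of 60, odds ratios 1, 1.2, 1.5, 1.8 and 2.2, same base distribution.** Chi-square: λ = 7.29 on 16 degrees of freedom, power 32%. Kruskal-Wallis: λ = 7.24 on 4 degrees of freedom, power 56%. Simulation agrees: 31% for chi-square and 54 to 57% for Kruskal-Wallis in separate runs. ANOVA on the scores 1 to 5 gives 55%.

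**Step 3: smaller and larger shifts, 60 vs 60, same base (simulated chi-square vs rank test).** OR 1.5: 13% vs 23 to 24%. OR 2: 34 to 35% vs 54 to 57%. OR 2.5: 57 to 58% vs 80%.

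**Step 4: other item shapes (4,000 runs each).** Shapes: symmetric 10/20/40/20/10%, skewed 3/5/12/25/55%, very skewed 1/2/4/13/80%, bimodal 35/10/10/10/35%. The five-group shifts are −0.5, −0.25, 0, 0.25 and 0.5 on the log-odds scale.

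| Comparison | Shape | Chi-square | ANOVA | Rank test | Rank − chi-square (points) | Rank − ANOVA (points) |
|---|---|---|---|---|---|---|
| 5 × 60 | symmetric | 0.493 | 0.767 | 0.774 | 28.1 | 0.7 |
| 5 × 60 | skewed | 0.435 | 0.664 | 0.719 | 28.4 | 5.5 |
| 5 × 60 | very skewed | 0.220 | 0.368 | 0.451 | 23.1 | 8.3 |
| 5 × 60 | bimodal | 0.498 | 0.770 | 0.768 | 27.0 | −0.2 |
| 900 vs 100, OR 1.7 | symmetric | 0.594 | 0.788 | 0.798 | 20.4 | 1.0 |
| 900 vs 100, OR 1.7 | skewed | 0.398 | 0.621 | 0.701 | 30.3 | 8.0 |
| 900 vs 100, OR 1.7 | very skewed | 0.112 | 0.314 | 0.397 | 28.5 | 8.3 |
| 900 vs 100, OR 1.7 | bimodal | 0.566 | 0.781 | 0.784 | 21.8 | 0.3 |
| 60 vs 60, OR 2.2 | symmetric | 0.414 | 0.638 | 0.645 | 23.1 | 0.7 |
| 60 vs 60, OR 2.2 | skewed | 0.332 | 0.510 | 0.562 | 23.0 | 5.2 |
| 60 vs 60, OR 2.2 | very skewed | 0.150 | 0.268 | 0.334 | 18.4 | 6.6 |
| 60 vs 60, OR 2.2 | bimodal | 0.428 | 0.635 | 0.639 | 21.1 | 0.4 |

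**Step 5: type I error.** With no true difference in these same settings, ANOVA rejected in 4.4 to 5.5% of runs and chi-square in 2.8 to 5.8%. The low chi-square values come from sparse cells in very skewed items.

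**The case against.** The best defence has three parts.

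First, section 2.7 says that the method depends on the type of data, and a condensed article may leave the mapping of item to test to a fuller plan. That is fair as far as it goes. But section 2.7 goes on to state a rule, and that rule has no place for a response format that section 2.5 says both questionnaires contain.

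Second, nothing assigns Likert items to chi-square. This stands: if they are scored and analysed by ANOVA, almost all of the loss disappears. The point is therefore conditional.

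Third, the study is exploratory, with descriptive p-values. That lowers the stakes but does not remove the loss in the comparisons that section 2.7 lists. It is also true that chi-square can pick up differences that are not shifts, such as one group being more polarised, which a rank test may miss. The category percentages already planned would show those.

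A reader might infer more than the document supports:
- **That the named tests give wrong p-values.** For between-group Likert comparisons they do not (step 5). Errors would arise if one respondent's ticks or ranks were pooled as if independent, and no section plans that.
- **That the primary ranking of information sources cannot be analysed.** Section 3.1 says "All findings will be based on the frequency and prevalence of collected responses", so a descriptive ranking meets the stated aim. A between-group ANOVA on one source's rank is also valid (4.7% rejection with no true difference).
- **That multiple-choice items break the chi-square test.** The article does not say that these are tick-all-that-apply items or how they are tabulated. Taken option by option, chi-square is valid (4.5 to 5.1% rejection), and the planned logistic regression also applies.

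**Conclusion.** The point holds as a conditional loss of efficiency. If Likert items are treated as categorical, chi-square gives up about 18 to 30 percentage points of power against a rank test over the moderate shifts examined, and about 10 points at an odds ratio of 1.5, where both tests are weak. For five professions of 60 the example is about 31% against 55%. If the items are scored and analysed by ANOVA, the loss is 0 to 8 points, the larger values being for skewed items. Type I error is not the problem in either case.

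The direction was the same in every setting tried. The size rests on assumed item shapes, proportional-odds shifts and alpha of 0.05, none of which the document gives. The share of Likert items cannot be checked without the questionnaires. The change is worth making because it is nearly free and settles the classification in advance; it does not put the study's validity in doubt.

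**What to change.** In section 2.7, state that ordered (Likert) items will be compared between groups with the Mann-Whitney test (two groups) or the Kruskal-Wallis test (more than two), with proportional-odds regression where adjustment for background characteristics is wanted. Keep chi-square for unordered categories, ANOVA for truly continuous variables and logistic regression for yes/no outcomes.

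As a clarification only, the same paragraph could say that rankings are summarised by mean rank and share ranked first, and that any multiple-response item is analysed option by option.

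The cost is a sentence or two of text, a few more lines of analysis in R or SPSS, which the plan already names, and slightly less familiar output. No new data and no change in sample size are needed.

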
Research gaps concerning the administration of DS, the consistency of taking them and compliance shall be closed by statistically evaluating data from performed surveys (vegans, pediatricians, gynecologists, general practitioners, pharmacists, and dieticians). In addition, causes for the intake or rejection of DS (from a social and socio-demographic perspective) are to be examined. Resulting risks concerning the supply of nutrients are to be determined as well as the role that information sources play in this context. It is precisely these unanswered questions that underline the relevance of the VedieS study, as they are directly related to risk prevention. According to a recent study by Meulenbroeks et al. [61], pregnant women following a vegan diet often receive limited or no specific dietary guidance from obstetric healthcare providers. Only 19% of participants reported having received nutritional counseling that was specific to their needs during pregnancy. The VedieS study’s approach to identifying the cause of nutrient deficiencies during vegan pregnancy and childhood, due to a fundamental lack of information, is new and can be important for preventing health risks for vegans. Unsupplemented vegan pregnancies are associated with a higher risk of adverse outcomes [45]. These findings highlight the importance of guideline-based supplementation for vegans during sensitive life stages. The quality of the information sources used by vegans is most likely dependent on the existing attitude of the information providers. If medical experts have a negative attitude towards a vegan diet and DS, their advice may be inadequate—either due to a lack of knowledge about a purely plant-based diet, or because a vegan diet is discouraged per se without providing additional information. Knowledge gaps regarding vegan diets remain common among medical experts, likely due to limited nutrition education and a lack of familiarity with plant-based dietary patterns [44,60]. As a result of limited professional support, many vegan pregnant women turn to alternative sources of information such as books, online platforms, or peer communities to address their specific dietary needs [61]. It is important to know exactly where the information received comes from in order to be able to draw conclusions about its safety and reliability. In a cross-sectional online survey by Fuschlberger et al. [62] among Austrian vegans, 92% reported taking vitamin B_12_ through DS or fortified foods, yet fewer than 10% had consulted a medical expert. However, more research is needed to find out exactly which specific sources of information are being used.

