### 5.2. Limitations and Strengths of the Study

Since the study is based on survey responses, there is a possibility of over- or under-reporting due to the subjective self-assessment of participants regarding, e.g., compliance when taking DS, parental administration consistency and correct dosage of DS, the frequency of exceptions to a vegan diet, and the period within parents and children already follow a vegan diet. Data is based on participants’ motivation to self-report. Hence, only responses from actual participants are considered which does not necessarily capture the opinion of all vegans and medical experts. Although all genders are included, it is likely that women will be overrepresented, because of the focus on pregnant/breastfeeding women and secondarily vegan parents. Nonetheless, the strengths of this study outweigh its limitations. This is the first time data has been collected considering perspectives of both vegans and different medical specialists regarding a vegan diet and DS during pregnancy and childhood. Resulting insights could help to shift experts’ attitudes from rejection of a fully plant-based lifestyle and the refusal of information provision on a vegan diet and DS during these life stages to more comprehensive, informed guidance for vegans. Experts’ acceptance of the need and the willingness for detailed advice can be promoted which could cause distancing from devaluing a vegan lifestyle. The value of gathering these fresh data on public health nutrition ultimately outweighs limitations as results provide significant benefits to both vegans and medical experts alike.

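### Section 2.7 names plain ANOVA for continuous variables; where self-formed groups differ in both size and spread its 5% rejection rate is off, and Welch's form would avoid this at almost no cost

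*Protocol article*

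**What the plan says.** Section 2.7 of the protocol article gives one rule for group comparisons: "Categorical variables will be analyzed using chi-square tests, and continuous variables with ANOVA". It names no form of ANOVA, no check of the variances and no alternative. The regression models in that section are logistic and serve yes/no outcomes, so ANOVA is the only method named for comparing continuous variables.

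The possible comparisons among vegans include "Supplement users vs. non-users (for themselves or their children" and those with professional advice against those who relied on informal sources. Gender is not on that list. Gender differences are a secondary objective in 2.1.2, however, and 2.7 leaves room for further comparisons.

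On sizes, the vegan survey has a planned total, "resulting in a target sample of 1000 vegan participants", but no planned split. For experts, "the aim is to recruit approximately 60 participants per expert group (pediatrics, gynecology, general medicine, pharmacy, dietetics". On error rates, 2.6.1 states that "no formal power calculation (e.g., based on alpha level, statistical power, or expected effect size) was carried out", and 2.7 adds: "Since the study is exploratory, *p*-values will be reported descriptively".

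Two places hint at imbalance. The Discussion cites a survey of Austrian vegans in which "92% reported taking vitamin B_12_ through DS or fortified foods, yet fewer than 10% had consulted a medical expert". Section 5.2 says of this study that "it is likely that women will be overrepresented".

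**The concern.** The ordinary ANOVA F test uses one variance pooled over all groups. When one group is far larger, that pooled value is close to the large group's own variance. The uncertainty of the comparison, however, comes mostly from the small group's mean. If the small group is more variable than the large one, the standard error is too small and false differences appear too often. If it is less variable, the standard error is too large and real differences are missed. At a fixed split and SD ratio, a larger sample does not cure this.

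At stake is the meaning of the p-values and intervals for numeric variables such as age, household size or duration of the vegan diet, listed among the secondary outcomes in 3.2. A descriptive p-value is still read against its nominal scale, and 2.7 plans no correction for multiple testing that might hold back false signals.

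**Working it through.** **The plan's own figure.** The article sets no alpha, power, SD or group split for any ANOVA comparison, so there is no error rate to reproduce. The vegan target follows from 25% of 4000 families: 0.25 × 4000 = 1000, which is the upper end of the 2000–4000 range. It does not bear on this point.

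**Inputs.**
- Method: ANOVA, read as the pooled-variance test (2.7).
- Splits: 92:8, suggested by the vitamin B12 figure in the Discussion; 80:20, close to the 19% of pregnant women in another cited study who had counselling specific to their needs; 70:30 as a milder case. None is a figure for this study.
- SD ratio r (smaller group's SD divided by the larger group's): 1.5 and 2/3. This is an assumption, as the documents give no SDs.
- Nominal level: two-sided 5%, also an assumption.

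**Formulas.** Let f be the share of the smaller group and set the larger group's SD to 1. Up to the same factor 1/N:
- true variance of the mean difference: V_true = r²/f + 1/(1−f)
- variance used by the pooled test: V_pooled = (f·r² + 1 − f) × (1/f + 1/(1−f))
- actual rejection rate with no true difference: 2 × [1 − Φ(1.96 × √(V_pooled/V_true))]

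**Worked case, 92:8, r = 1.5.** V_true = 2.25/0.08 + 1/0.92 = 28.125 + 1.087 = 29.21. V_pooled = (0.18 + 0.92) × (12.5 + 1.087) = 1.10 × 13.587 = 14.95. The ratio is 0.512 and its root 0.715, so the effective critical value is 1.40 and the rejection rate 16.1%.

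**Same split, r = 2/3.** V_true = 0.4444/0.08 + 1.087 = 6.64. V_pooled = 0.9556 × 13.587 = 12.98. The root of the ratio is 1.398, the critical value 2.74, and the rejection rate 0.61%.

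**All splits, formula.**

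| Split | r = 1.5 | r = 2/3 | r = 1 |
|---|---|---|---|
| 92:8 | 16.1% | 0.61% | 5.0% |
| 80:20 | 12.1% | 1.3% | 5.0% |
| 70:30 | 9.3% | 2.2% | 5.0% |
| 50:50 | 5.0% | 5.0% | 5.0% |

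With r = 1.25 or 0.8 at 92:8 the rates are 10.4% and 1.8%.

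**Simulation check** (normal data, no true difference; 10,000 data sets per setting, 20,000 for 240 vs 60).

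| Groups | r | Pooled | Welch |
|---|---|---|---|
| 920 vs 80 | 1.5 | 16.0% | 5.1% |
| 920 vs 80 | 2/3 | 0.5% | 4.9% |
| 240 vs 60 | 1.5 | 12.0% | 5.0% |
| 240 vs 60 | 2/3 | 1.5% | 5.0% |
| 700 vs 300 | 1.5 | 9.0% | 4.5% |
| 700 vs 300 | 2/3 | 2.3% | 5.3% |

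Over all splits and SD ratios tried (r from 0.5 to 2), Welch's test stayed between 4.5% and 5.4%.

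**Professions at 60 each.** The simulated five-group pooled ANOVA rejects 5.0% with equal SDs, 5.5% with one SD at 1.5, 6.2% with SDs spread from 0.67 to 1.5, and 7.0% with one SD at 2.

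**The case against.** The strongest reply is that the article contains no error. It says ANOVA, not equal-variance ANOVA. Welch's ANOVA is an ANOVA, and an analysis plan that is not shown may specify it. This stands as far as it goes: the pooled form is the ordinary reading, not a stated fact. But the article does fix the method by name for every continuous variable, so naming the safer form improves a choice already made rather than asking for missing detail.

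The second reply is that the sizes rest on borrowed inputs. This also stands. The 92% counts fortified foods as well as supplements and comes from Austrian vegans in general, so it is only a proxy for supplement use. The advice comparison in 2.7 is against users of informal sources, not against everyone else, and the 19% counselled figure comes from a population closer to this one. Even so, at 80:20 the assumed SD ratios still give 12.1% or 1.3%.

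Third, little is exposed. Section 3.1 bases the primary findings on frequencies, most questionnaire items in 2.5 are Likert, choice or ranking items, no alpha is set, p-values are descriptive, and comparisons are made only where the data suffice. All of this stands, and it is why the point is minor.

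A reader might infer that all comparison groups in 2.7 will be badly unbalanced, or that imbalance by itself invalidates ANOVA. The documents support neither. The professions are planned at equal size, no split is given for rural/urban, diet changers or supporters/rejecters, and with equal SDs the rate is 5% at any split.

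**Conclusion.** The point holds as a minor, cheap improvement. Read in the ordinary way, ANOVA in 2.7 is vulnerable wherever a numeric variable is compared between groups that differ in both size and spread. Imbalance is plausible for supplement use, professional advice and gender. Whether the spread differs is unknown.

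With an assumed SD ratio of 1.5 or two-thirds, the nominal 5% becomes about 16% or 0.6% at 92:8, 12% or 1.3% at 80:20, and 9% or 2% at 70:30. Welch's test keeps it near 5% throughout. The comparison of professions is little affected (5% to 7%) if the planned 60 per group is reached.

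It is tempting to say that the p-values will be three times too liberal or ten times too strict. That goes too far. These factors describe rejection rates at 5%, not p-values as such. At 92:8 they are 16.1/5 = 3.2 and 5/0.61 = 8.2, and a factor of about ten needs a 95:5 split (0.49%). Both require an SD ratio that the documents do not give. The frequency-based primary findings and the logistic models are untouched.

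**What to change.** In 2.7, replace ANOVA by Welch's (unequal-variance) ANOVA for continuous variables, and state that mean differences will be reported with unequal-variance 95% confidence intervals.

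This is a change of wording. It needs no new data and no change to the sample, and the method is available in both programs that 2.7 names, SPSS and R. The only downside is a negligible loss of power if the variances turn out equal.
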